## Labeling and Coding

The aluminum pouch containing the test supplement (for 30 days) will be labelled either A or B. A randomization will achieved by envelope containing a card printing either A or B at the enrollment. The sponsor keeps the key in a sealed envelope until the key open.

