# STUDY DESIGN

This is a single-center, randomized, double-blind, placebo-controlled, 2-arm parallel group study. This study will consist of a 30 days administration period.

The planned sample size for this study is 50 healthy older adults, with 25 subjects randomized equally to each of the two-study arms in a double-blind manner.

| **Study Arm** | **Subject Number** |
| --- | --- |
| Krill Oil | N = 25 |
| Placebo | N = 25 |
| **Total** | **N = 50** |

In order to evaluate the goals of the study, assessments will be conducted at Visit 1 (Day 1) before administration of the test supplement (baseline), and Visit 3 (Day 31). Subject will visit or will be contacted by phone after 2 weeks of ingestion (Visit 2) in order to monitor adverse events and changes in concomitant medications as well as to foster compliance with the study dosing regimen.

The study will be conducted at a single site at Fukushima Orthopedic Clinic, Tochigi, Japan.

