## Unblinding and Allocation Concealment

Unblinding should not occur except in the case of emergency situations. In the event that a serious adverse event occurs, for which the identity of the test supplement administered is necessary to manage the subject’s condition, the treatment received by the subject will be unblinded and the test supplement identified. The sponsor must be notified and unblind the key within 24 hours.

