### JKOM and JOA

Subjects will fill JKOM questionnaire by his/her own.

Orthopedist will fill JOA score list interviewing subject.

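### Two shared codes (A and B) under one key mean that emergency unblinding of one subject discloses the arm of all 50 to any staff who know the letters

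*Protocol*

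**What the plan says.** The Study Design section describes the trial in these words: "This is a single-center, randomized, double-blind, placebo-controlled, 2-arm parallel group study". On size it says: "The planned sample size for this study is 50 healthy older adults, with 25 subjects randomized equally to each of the two-study arms".

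Labeling and Coding sets the coding scheme. For the pouches: "The aluminum pouch containing the test supplement (for 30 days) will be labelled either A or B". For allocation: "A randomization will achieved by envelope containing a card printing either A or B at the enrollment". For the key: "The sponsor keeps the key in a sealed envelope until the key open". No subject-specific kit number, no set of several codes per arm and no individual code-break envelope is described.

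Unblinding and Allocation Concealment covers a serious adverse event in which the product must be known to manage the subject. In that case "the treatment received by the subject will be unblinded and the test supplement identified", and the means is: "The sponsor must be notified and unblind the key within 24 hours".

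Both primary outcomes are subjective. According to JKOM and JOA, subjects complete the JKOM themselves, and for the other: "Orthopedist will fill JOA score list interviewing subject".

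**The concern.** The emergency rule is written for one subject, but the coding scheme has no subject-level code to break. Once the site is told what one subject's letter stands for, it knows what both letters stand for. Anyone there who has opened the cards or handed out the pouches can then classify every subject.

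The shared letter also creates a slower route that needs no formal break. Everyone on a product carries the same visible mark, so impressions from different subjects can be set side by side by letter. With unique numbers there would be nothing to pool by.

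What is at stake is mainly the JOA. It is a primary outcome, scored by interview at the one clinic where the supplement is also stored (Manufacturing and Storage). The protocol does not say that the orthopedist is kept from the letters. If the rater learns what they mean, ratings still to be made can drift towards the expected result. The JKOM is affected by this route only if the inference is passed on to subjects.

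**Working it through.** The plan states no figure on this point, so there is none to reproduce. The check has three parts.

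**1. How far one code break reaches**

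Inputs: 50 subjects, 25 per arm (Study Design); two letters and one key (Labeling and Coding); unblinding by opening the key (Unblinding and Allocation Concealment).

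- Two shared letters: knowing one letter's meaning fixes the other, so 50/50 = 100% of allocations are disclosed to a person who knows the letters.
- Unique subject codes with subject-level code breaks: 1/50 = 2%.
- Excess disclosure: 50 − 1 = 49 subjects.

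**2. How clues pool under a shared letter**

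Assume that each subject gives one independent clue pointing to the right product with probability p. The protocol gives no basis for p, so a range is shown. The chance that a majority of n clues (n odd) identifies the letter is P(X ≥ (n+1)/2), with X ~ Binomial(n, p):

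| p (assumed) | n = 11 | n = 25 | n = 49 |
|---|---|---|---|
| 0.55 | 63% | 69% | 76% |
| 0.60 | 75% | 85% | 92% |
| 0.70 | 92% | 98% | 99.8% |

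Weak clues add up because they share a letter. Even so, the result is a belief that nobody at the site can verify while the key stays sealed.

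**3. What a rating shift would do to the false-positive rate**

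Inputs: n = 25 per arm (Study Design). Two assumptions are added: a two-sided 5% t test with no true effect, and a spurious between-arm shift d in SD units.

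Formula: noncentrality = d × √(n/2) = d × √12.5 = d × 3.536, with 48 degrees of freedom. The rejection rate is the probability that the noncentral t falls outside ±2.011.

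If the shift affects every Visit 3 rating:
- d = 0.2: noncentrality 0.707, rejection rate 10.7%
- d = 0.3: noncentrality 1.061, rejection rate 18.0%

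A break can bias only ratings made after it. If half of them follow the break, the average shift is halved:
- d = 0.2 × 0.5 = 0.10: noncentrality 0.354, rejection rate 6.4%
- d = 0.3 × 0.5 = 0.15: noncentrality 0.530, rejection rate about 8%

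**The case against.** The case on the other side has real force.

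- **A guess is not a code break.** A reader might infer that one correct guess unblinds the whole trial. The documents do not support that. The key is sealed with the sponsor, so a guess stays unconfirmed, and it reaches other subjects only through someone who knows their letters. This objection stands.
- **JKOM.** A reader might also infer that both primary outcomes are equally exposed. A subject who guesses from the capsules learns only his or her own arm, and could do so under any labelling. The shared letter adds risk to the JKOM only if subjects compare letters or staff pass on what they believe, and the text describes neither. This stands.
- **Rater exposure is inferred.** The protocol does not say that the orthopedist opens cards, hands out pouches or sees letters. Nor does it say otherwise. The link is plausible at a single clinic but not established.
- **The letter may not be the only mark.** The text does not exclude a further identifier on the pouch. That would not help while the letter remains visible.
- **A formal break may be rare, and its audience is not specified.** The safety section does not expect serious adverse events, and the unblinding section does not say who is told. It is therefore too strong to say that a single-subject break must compromise the whole trial. The harm requires that the meaning reaches people who know other subjects' letters and have ratings still to make.
- **Taste or smell.** The protocol reports no such difference between the capsules. It does not say that they match either, so p in the table is purely an assumption.

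These points narrow the concern and lower its weight, particularly for a pilot with 30 days of administration. None of them supplies the missing subject-level code break.

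**Conclusion.** The point holds in a limited form. The protocol fixes two shared codes under one key and foresees single-subject unblinding by opening that key. Nothing elsewhere in the document reconciles the two. One break discloses 50 of 50 allocations, instead of 1 of 50, to staff who know the letters. Pooling of clues by letter is a further weakness, but it gives belief, not certainty.

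The likely harm is to JOA ratings made after the meaning is known, on condition that the orthopedist can learn the letters. The false-positive rates of about 11–18% (all Visit 3 ratings affected) and about 6–8% (half affected) are illustrations. They rest on an assumed shift of 0.2 to 0.3 SD that has no source in the protocol, and they do not include the probability that a break occurs.

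This should be fixed, and before pouches are labelled, because disclosure cannot be undone. The documents do not show that the blind will be lost or that the trial would be uninterpretable.

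**What to change.** In Labeling and Coding, replace A and B on pouches and cards with unique kit or subject numbers. Draw them from a randomisation list held by the sponsor or another party away from the site's assessors, and assign the next numbered kit at enrolment. Prepare one sealed code-break envelope per subject. Reword the mechanism in Unblinding and Allocation Concealment so that a break opens only that subject's allocation. The circumstances in which unblinding is allowed need not change.

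Cost: about fifty individual labels, about fifty envelopes and the upkeep of a list. No subject, visit or assessment is added.

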## Test supplements

Soft-capsule

| # | Product | Ingredient |
| --- | --- | --- |
| 1 | Placebo | safflower oil (Nisshin Oillio Group)  （250mg/capsule） |
| 2 | Krill Oil | Superba^TM^ Krill Oil  （250mg/capsule） |

## Directions

Subjects will be instructed to take 8 capsules daily, 4 capsules in the morning with breakfast and 4 capsules in the evening with dinner. Subjects will be instructed to start taking the product the day taking the baseline examination (Day 1).

## Unblinding and Allocation Concealment

Unblinding should not occur except in the case of emergency situations. In the event that a serious adverse event occurs, for which the identity of the test supplement administered is necessary to manage the subject’s condition, the treatment received by the subject will be unblinded and the test supplement identified. The sponsor must be notified and unblind the key within 24 hours.

# STUDY ASSESSMENTS

See Appendix 1 for the schedule of assessments and procedures.

## Visit 1 – Screening and enrollment

At screening, a Subject Information and Consent Form will be given to the potential subject. The subject will read the information carefully and will be given the opportunity to seek more information if needed. The subject will also be provided with the option of taking the consent form home to review prior to making his or her decision. If agreeable, the subject will sign the consent form and receive a duplicate. Once consent has been obtained, the following assessment will proceed.

- Review of the inclusion/exclusion criteria
- Review of medical history and concomitant therapies
- Collection of demographic information such as gender, age, alcohol consumption and smoking habits

Eligible subjects will be randomized and take baseline assessment.

Baseline assessments will include:

- Height, weight and BMI
- Japanese Knee Osteoarthritis Measure (JCOM)
- The Japanese Orthopedic Association knee rating score (JOA score)
- Blood and Urine analysis
- Range of motion (ROM) of the knee

Subjects will receive test supplements and administration diary.

Subjects will be instructed in detail by site personnel about the dosing regimen. The first dose of study product is to be taken the day at the dinner on the day taking the baseline assessment (Day 1).

## Visit 2 – Week 2 (Day 14 ± 3)

Subjects will return to the clinic and the following will be discussed to reinforce product compliance:

- review of current conditions, concomitant therapies and adverse events
- compliance with test supplement

The Visit 2 can be performed via phone call.

## Visit 3 – Week 8 End of Study (Day 31: 29 - 37)

Subjects will return to the clinic on day 31; Day 29– 37 will be possible according to the convenience of the subject.

Remaining test supplement in the original packaging will be returned.

Visit 3 assessments will include:

- concomitant therapies
- any adverse events
- Japanese Knee Osteoarthritis Measure (JCOM)
- The Japanese Orthopedic Association knee rating score (JOA score)
- Blood and Urine analysis
- Range of motion (ROM) of the knee
- Study diaries will be collected and reviewed.

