# STUDY OBJECTIVES

To examine the effect of a 30 days (approximately 4 weeks) of krill oil administration on knee joint pain.

Primary outcomes**:**

- Japanese Knee Osteoarthritis Measure (JCOM)
- The Japanese Orthopedic Association knee rating score (JOA score)

Secondary outcomes**:**

- Blood and urine analysis
- Range of motion (ROM) of the knee

* ROM was deleted from the secondary outcome because of the difficulty to obtain the reliable data.

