# APPENDICES

## Appendix 1 Schedule of Assessments

|  | **Visit 1** | **Visit 2** | **Visit 3** |
| --- | --- | --- | --- |
| DAY | **1** | **15** | **31** |
| PLACE | **clinic** | **Clinic or phone call** | **Clinic** |
| Informed Consent | X |  |  |
| Review inclusion/exclusion criteria | X |  |  |
| Review medical history | X |  |  |
| Review concomitant therapies | X | X | X |
| Randomization | X |  |  |
| Height, weight, and BMI calculated. | X |  |  |
| Range of motion of the knees | X |  |  |
| Japanese Knee Osteoarthritis Measure (JCOM) | X |  | X |
| The Japanese Orthopedic Association knee rating score (JOA score) | X |  | X |
| Laboratory Test: Blood | X |  | X |
| Laboratory Test: Urine | X |  | X |
| Test supplement Dispensed | X |  |  |
| Administration diary dispensed | X |  |  |
| Test supplement returned |  |  | X |
| Administration diary returned |  |  | X |

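### The only outcome visit may fall up to Day 37, but the single 30-day supply runs out at breakfast on Day 31, so full compliers seen on Days 32–37 are assessed 1 to 6 days off supplement

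*Protocol*

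**What the plan says.** The objective is stated as "To examine the effect of a 30 days (approximately 4 weeks) of krill oil administration on knee joint pain", and the Study Design section says "This study will consist of a 30 days administration period". The same section places outcome assessment at two times only, baseline and Visit 3, the latter nominally on Day 31. Visit 2 covers adverse events, concomitant therapies and compliance, and may be a phone call.

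On supply, Labeling and Coding describes one pouch per subject, holding 30 days of supplement. The row "Test supplement Dispensed" in Appendix 1 is marked at Visit 1 and nowhere else. The Directions prescribe "8 capsules daily, 4 capsules in the morning with breakfast and 4 capsules in the evening with dinner". The Visit 1 section fixes the first dose at dinner on Day 1, after the baseline assessment.

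On timing, the Visit 3 section names Day 31 and then says that any day from 29 to 37 "will be possible according to the convenience of the subject". The Compliance section adjusts the expected capsule count only for a visit before Day 31. Nothing in the protocol tells a subject with a later visit whether to go on dosing, or with what.

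**The concern.** The supply and the visit window were set separately and do not match. The pouch fits the nominal Day 31 visit exactly, but the window runs 6 days beyond it and only 2 days before it. A subject who takes every dose and comes late is measured after dosing has stopped.

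This matters because there is no other post-baseline value to use. JKOM, JOA and the laboratory outcomes, including plasma EPA and DHA (the variables behind the sample-size choice), are all measured at Visit 3 alone. The effectiveness analysis is per protocol and excludes subjects below 80% compliance, so it selects for adherence, and the most adherent subjects are the ones who run out first. If a benefit fades after the last dose, late visits shrink the contrast the trial is meant to show, and with 25 subjects per arm there is little room for avoidable loss.

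An analysis plan cannot repair this. Visit date and diary should allow days since last dose to be derived for each subject, but they do not supply an on-supplement measurement.

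**Working it through.** **Inputs**

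- Supply: 30 days, dispensed once at Visit 1 (Labeling and Coding; Appendix 1).
- Dose: 4 capsules at breakfast and 4 at dinner, 8 a day (Directions).
- First dose: dinner on Day 1 (Visit 1).
- Visit 3: Day 31 nominal, Days 29–37 permitted (Visit 3).
- Assumption: the pouch holds exactly 30 × 8 = 240 capsules. The protocol states neither a capsule count nor an overage.

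**When the supply ends**

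- Day 1, dinner: 4.
- Days 2–30: 29 × 8 = 232, running total 236.
- Day 31, breakfast: 4, running total 240.

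The last dose is breakfast on Day 31, which agrees with the nominal visit day.

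**Capsules needed to dose through breakfast on visit day d**

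Need(d) = 4 + 8(d − 2) + 4 = 8(d − 1). After Day 31, shortfall = 8(d − 1) − 240 and gap = d − 31 days.

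| Visit day | Capsules needed | Shortfall | Days since last dose |
|---|---|---|---|
| 29 | 224 | 0 | 0 |
| 31 | 240 | 0 | 0 |
| 32 | 248 | 8 | 1 |
| 33 | 256 | 16 | 2 |
| 34 | 264 | 24 | 3 |
| 35 | 272 | 32 | 4 |
| 36 | 280 | 40 | 5 |
| 37 | 288 | 48 | 6 |

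The window has 37 − 29 + 1 = 9 days, and 6 of them (Days 32–37) fall after the supply has ended. These are calendar days, not a proportion of subjects.

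**Subjects who miss doses**

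At 80% of the daily dose (6.4 capsules) the pouch lasts 240 / 6.4 = 37.5 days; at 90% (7.2 capsules) it lasts 240 / 7.2 ≈ 33 days. Such subjects could have a shorter gap or none if they kept dosing after Day 31, though no instruction tells them to. The gaps in the table are those of a full complier.

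**The case against.** The strongest reply is that the protocol describes a fixed 30-day course. Objective, administration period, pouch and scheduled visit agree, and nothing requires subjects to be on supplement at the moment of assessment. A late allowance is an ordinary way to avoid losing subjects, and it has value here: the per-protocol population requires all visits to be completed, and subjects who leave early are not replaced.

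The reply also points out that materiality is not shown. The protocol does not say that any benefit fades within 1 to 6 days, most visits may well fall near Day 31, and both arms are treated alike. Finally, extending the supply replaces a nearly constant exposure with one set partly by the subject's convenience.

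Much of this stands. The consequence is conditional and of unknown size, Day 37 is the extreme, and the finding applies to full compliers. The wish to keep late attenders is a good reason not simply to cut the window. What does not follow is that the mismatch is harmless. The protocol gives no basis for assuming that an effect persists after the last dose, and its text leaves late attenders without supply or instruction. The exposure trade-off is real but small, and it can be stated openly in the objective.

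**Conclusion.** The concern holds. Followed as written, the protocol lets the only outcome assessment take place 1 to 6 days after a full complier's last dose, on 6 of the 9 permitted days. There is no gap on Days 29–31.

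The timing result rests on two conditions: the pouch contains no overage, and the subject takes every dose. The expected consequence is dilution of a benefit that fades, not a false positive. Its size cannot be computed, because the protocol gives neither the expected share of late visits nor how quickly an effect would wane. This does not invalidate the trial, but it is an avoidable weakness that should be corrected because correction is so cheap.

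**What to change.** Keep the window and extend the supply to cover it.

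- Dispense 288 capsules at Visit 1 (4 on Day 1, 35 × 8 = 280 on Days 2–36, 4 at breakfast on Day 37).
- Instruct subjects to keep dosing through breakfast on the day of Visit 3.
- For the 80% compliance cut, count expected capsules as 4 per scheduled meal from dinner on Day 1 to the visit. This must go with the larger supply: if 240 stayed the expected number, a subject seen on Day 37 would pass with 0.8 × 240 = 192 capsules out of 288 scheduled, or 67%. That problem would arise only from changing the supply without the denominator; it is not a fault of the current text.
- Reword the objective to say about 30 days of administration.

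The cost is 288 − 240 = 48 more capsules per subject, 48 × 50 = 2,400 in all, and a few lines of wording. Exposure of full compliers would range from about 28 days (224 / 8) to 36 days (288 / 8), instead of 28 to 30 now.

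If the sponsor prefers a fixed 30-day exposure, ending the window at Day 31 also removes the gap for full compliers and needs no extra capsules. It risks losing analysable subjects who cannot attend by then, so the first option is preferable.

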## Clinical Assessments and Procedures

### Height, Weight and BMI

Measurement of weight and height will be performed with the subject's shoes removed, and bladder empty.

BMI will be calculated from weight and height.

### JKOM and JOA

Subjects will fill JKOM questionnaire by his/her own.

Orthopedist will fill JOA score list interviewing subject.

### Range of motion of the knee

Orthopedist will measure range of motion of the knees of subject.

### Compliance

Compliance will be assessed by counting the returned supplements at Visit 3. Compliance is calculated by determining the number of capsules taken divided by the number of capsules expected to have been taken multiplied by 100.

$$\frac{number of capsules taken}{number of capusles expected to have been taken} \times100\%$$

In the event of a discrepancy between the information in the subject diary and the amount of study capsules returned, use will be based on the capsules returned unless an explanation for loss of capsules has been provided.

If Visit 3 comes before Day 31, compliance will be calculated dividing the number of the capsules taken by the number of the capsules expected to have been taken during Day 1 to Visit 3 (8 capsules per day).

## Laboratory Analysis

Blood and urine samples will be collected at Visit 1 and Visit 3.

The following parameters will be analyzed.

### Blood count

- white blood cell (WBC)
- red blood cell (RBC)
- hemoglobin (Hb)
- hematocrit (Ht)
- platelet (PLT)
- mean cell volume (MCV)
- mean cell hemoglobin (MCH)
- mean cell hemoglobin concentration (MCHC)

### Serum parameters

- aspartate transaminase (AST)
- alanine aminotransferase (ALT)
- γ-glutamyl transpeptidase (γ-GTP)
- uric acid (UA)
- urea nitrogen (UN)
- triglyceride (TG)
- total cholesterol (T-Cho)
- HDL-cholesterol (HDL-Cho)
- LDL-cholesterol (LDL-Cho)
- C-reactive protein (CRP)
- matrix metalloproteinase 3 (MMP-3)
- hyaluronic acid

### Plasma fatty acids

- arachidonic acid (AA)
- eicosapentaenoic acid (EPA)
- di-homo-γ-linoleic acid
- docosahexaenoic acid (DHA)

### Urine

- Urine specific gravity
- pH

LSI Medience Corp (Tokyo, Japan) will be used in this study to measure laboratory parameters.

The total blood volume collected for the laboratory assessments listed above will be approximately < 20 mL at a study visit.

